## **5.3 Subject Recruitment**

Subjects will be recruited internally through the UC Davis VMTH services and from targeted advertisements via referring hospitals, StudyPages, social media, and online listings. Dogs participating in this study will be privately owned.

## **5.4 Subject Screening**

### **5.4.1 Screening Procedures**

Patient medical records will be evaluated to determine eligibility. If the dog appears to meet preliminary inclusion criteria, a formal appointment/consultation (trials service) will occur. At which time, the owners will be given detailed information on the trial, including nebulization as well as standard therapy options. If interested, the owner will review the Informed Consent Form with trials staff and sign the document.

#### **5.4.1.1 Subject Re-screening**

If the PI and overseeing clinician determine that a patient may be eligible for re-screening at a later date (i.e. pulmonary nodules  $< 1$ cm, patient or client require additional time to acclimate to the nebulizer, etc.), this will be determined on a case-by-case basis where the inclusion/exclusion criteria still apply as described and additional required diagnostics would be at the owner's expense.

CONFIDENTIAL

This material is the property of the University of California Do not disclose or use except as authorized in writing by the study sponsor

#### 5.4.2 Determination of Eligibility

Determination of eligibility will be by the clinical trials clinician unless there are questions or concerns and then consultation with [name] will result in determination.

#### 5.4.3 Informed Consent

Informed consent will be obtained by the study coordinator or trials clinician at or prior to the Week 0 visit after the study clinician has confirmed preliminary eligibility. The informed consent form is attached as an appendix. A copy of the signed consent form will be provided to the owner, one copy will be scanned into the patient medical record in VMACS on the visit for Day 0, and the original signed copy will be kept in the patient study binder.

### 5.5 *Subject Identification*

Dogs will be identified by their given name and owner's surname, as recorded in their medical records. In addition, dogs will be identified by both their assigned by their unique medical record number in VMACS, and by a study number that will consist of UCD-followed by a 4-digit sequential number starting with the number 201. e.g. UCD-IL15Doxo-201, UCD-IL15Doxo-202, UCD-IL15Doxo-203, etc. The study number is assigned on Day 0.

### 5.6 *Subject Retention*

Standard visit reminders, phone calls between visits, e-mail check-ins, calls from the coordinators.

### 5.7 *Early Withdrawal of Subjects*

#### 5.7.1 When and How to Withdraw Subjects

Subjects may be withdrawn at the request of the caregiver, due to adverse events, and/or at the investigator's discretion. If any patient becomes increasingly sick, and the quality of life is of concern to the study staff, discussions will occur to determine how to proceed.

The investigator may remove the subject from the trial if their caregivers fail to bring them to scheduled study visits and/or provide data and the caregivers cannot be reached by the study site for 2 weeks. Alternatively, if caregiver cannot consistently give the patient the twice daily inhaled dose of IL-15, they may be removed from the study.

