#### 3.2 Primary Study Endpoints

Objective response rates based on radiographic response

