#### 5.7.2 Data Collection and Follow-up for Withdrawn Subjects

Request permission for follow up phone calls or emails relating to outcome data. UCD can provide prepaid shipping label for return of nebulizer and supplies.

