##### Start Inhaled IL-15 Therapy:

- Physical examination
- Quality of life assessment form
- 13 mL of blood obtained for CBC, Chem and PBMC's
- CBC evaluated by trials clinician
  - No minimum cell requirements for IL-15 administration, but if clinically unwell from doxo, may delay
- Inhaled IL-15 (50ug) started in hospital followed by 2 hours monitoring (See XXX section for monitoring details)
- 14 days' supply of IL-15, required PPE, IL-15 Administration Diary sent home with owner

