### 7.2.6 Follow-up – Visit Day 35 (+/- 3 days)

#### Response Evaluation, Bloodwork, & Monitoring:

- Physical examination
- Quality of life assessment form
- 11.5 mL blood will be collected for PBMCs and CBC
- Repeat thoracic radiographs

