#### 7.3.3 Subject Compliance Monitoring

Prior to discharge on Day -7 to -1 (screening) owners will be trained on proper use and handling of nebulizer and drug. Owners will go home with a paper copy of “Owner Administration Instructions for Inhaled IL-15” which includes links to training videos. Proper training will be documented on a training log. Owners will complete and return a “Daily Drug Administration Diary” logging Inhaled IL-15 treatments. Failing to comply with treatment regimens and scheduled visits will be grounds for discontinuation in the study.

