### 8.3 *Subject Population(s) for Analysis*

per-protocol/protocol compliant (starting inhaled IL-15)

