#### **9.4 Stopping Rules**

Study participant can be discontinued from trial participation:

- If deemed clinically indicated by the attending clinician
- If requested by the owner
- Owner non-compliance with treatments or visits

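### A dog removed from the trial for inconsistent IL-15 dosing before Day 35 has no planned film for the radiographic primary endpoint, because stopping the drug is not separated from leaving the trial

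*Protocol*

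**What the plan says.** Three sections of the protocol deal with a caregiver who does not manage the dosing:

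- Section 5.7.1: "if caregiver cannot consistently give the patient the twice daily inhaled dose of IL-15, they may be removed from the study".
- Section 7.3.3: "Failing to comply with treatment regimens and scheduled visits will be grounds for discontinuation in the study".
- Section 9.4, among the grounds on which trial participation can end: "Owner non-compliance with treatments or visits".

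For withdrawn dogs, the outcome-data provision in section 5.7.2 is "Request permission for follow up phone calls or emails relating to outcome data". No visit or film is mentioned there.

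The primary endpoint in section 3.2 is "Objective response rates based on radiographic response". Sections 6.2 and 7.2.3 start IL-15 at Day 7 for 14 days, with the first dose given on site: "Inhaled IL-15 (50ug) started in hospital followed by 2 hours monitoring". After the baseline film, the schedule in 7.1 has no thoracic radiograph until Day 35, where section 7.2.6 lists "Repeat thoracic radiographs". Another follows at Day 49.

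Section 8.3 describes the analysis population as "per-protocol/protocol compliant (starting inhaled IL-15", with the last phrase in parentheses.

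**The concern.** Dosing problems show themselves between Day 7 and about Day 21. A removal made because of them would normally come before the first response film. The dog has then received at least one dose of IL-15, but its primary outcome is never measured under the plan, and an owner cannot report a radiographic response by phone.

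Section 8.3 does not settle what happens next. Its parenthetical takes such a dog in, because it started IL-15; its protocol-compliant label could leave it out. An analysis plan can choose between these readings and can fix a rule for missing responses. It cannot recover a film that was not taken, and that part is a matter of trial conduct which the protocol itself fixes.

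At stake is whether a partly dosed dog keeps its response measurement. In an open-label trial of 10 dogs, that turns on an individual, unmasked decision.

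**Working it through.** **Inputs.** Section 8.1 gives a null response rate of 11%, an alternative of 50%, one-sided 0.05 and n = 10 with 80% power. The number of dogs removed before Day 35, m, is not in the protocol; m = 1 or 2 is an assumption. So is the response rate q of partly dosed dogs, shown at 11%, 25% and 50%.

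**1. The stated design.** Under the exact binomial, the cutoff is the smallest r with P(Bin(10, 0.11) ≥ r) ≤ 0.05.

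- r = 3: 0.0884, too large.
- r = 4: 0.0178, so 4 of 10 responders are needed.
- Power: P(Bin(10, 0.5) ≥ 4) = 0.828.

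This agrees with section 8.1 when its 80% is read as at least 80%.

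**2. Unfilmed dogs counted as failures, cutoff still 4 of 10.** Power is P(Bin(10 − m, 0.5) ≥ 4).

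- m = 1: 0.746. The type I error is P(Bin(9, 0.11) ≥ 4) = 0.012.
- m = 2: 0.637. The type I error is P(Bin(8, 0.11) ≥ 4) = 0.007.

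**3. The same dogs filmed instead.** Power is P(X + Y ≥ 4), with X ~ Bin(10 − m, 0.5) and Y ~ Bin(m, q).

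- For m = 1 the gain over step 2 is q × P(Bin(9, 0.5) = 3) = q × 84/512 = 0.164q.
- For m = 2 the gain is P(Y ≥ 1) × P(Bin(8, 0.5) = 3) + P(Y = 2) × P(Bin(8, 0.5) = 2) = [1 − (1 − q)²] × 0.219 + q² × 0.109.

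| q | m = 1: power (gain) | m = 2: power (gain) |
|---|---|---|
| 11% | 0.764 (0.018) | 0.684 (0.047) |
| 25% | 0.787 (0.041) | 0.739 (0.103) |
| 50% | 0.828 (0.082) | 0.828 (0.191) |

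**4. Unfilmed dogs dropped, cutoff re-derived for the smaller n.**

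| n | Cutoff | Type I error | Power at 50% |
|---|---|---|---|
| 10 | 4 | 0.018 | 0.828 |
| 9 | 4 | 0.012 | 0.746 |
| 8 | 3 | 0.049 | 0.855 |

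Power moves irregularly because the cutoff is a whole number. The conclusion can still change with the denominator: 3 responders of 10 gives P(Bin(10, 0.11) ≥ 3) = 0.088, while the same 3 of 8 gives P(Bin(8, 0.11) ≥ 3) = 0.049.

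**5. Extreme bound on the type I error.** Suppose both dropped dogs are always non-responders and the 3-of-8 cutoff is used. The test then rejects whenever at least 3 of the 10 would respond, which has probability 0.088 at a true rate of 11%. If removal is unrelated to response, the error of that rule is 0.049.

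**The case against.** The wording is permissive throughout. An investigator may keep a partly dosed dog on its visits, and section 5.7.2 does not forbid a film; one taken elsewhere might even reach the site. This stands: a reader might infer that the protocol obliges removal and so destroys data, and the text does not support that.

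Exposure is also limited. Exclusion criterion 1 rules out owners who cannot dose and dogs that cannot tolerate nebulization. Caretakers must demonstrate administration, and dogs are desensitized at home with saline first. Dosing lasts two weeks, and the diary comes back only at Day 21, although Day 14 and phone contacts can reveal problems earlier. This stands too, and the frequency is unknown. But three sections foresee failed dosing, and Appendix III warns that some dogs may be too anxious for the treatment.

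A reader might also infer that the investigator could remove dogs according to their response. Before Day 35 no follow-up film has been planned, so direct selection on the outcome is not supported. What remains is an indirect route, such as a deteriorating dog that resists the mask. That is plausible but undocumented, and the separate quality-of-life withdrawals would continue in any case.

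Finally, counting missing dogs as failures is conservative, and the choice of population and missing-data rule may sit in an analysis plan that is not shown. Both points are right. Neither supplies the missing film.

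**Conclusion.** The point holds in limited form, as a recommended improvement with medium confidence. For a dog removed between Day 7 and Day 35, the plan provides no measurement of the primary endpoint, and no later analysis rule can restore it.

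The size depends on assumptions the protocol cannot confirm: 1 or 2 removals in 10, an exact test, and a guessed response rate in partly dosed dogs. Under failure-counting, the cost is about 8 or 19 points of power. Filming recovers only a small part of that if these dogs respond at the null rate, and all of it only if they respond as well as fully dosed dogs.

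Two stronger conclusions are not supported. There is no fixed loss of power, because under exclusion power can fall or rise. Nor is the trial's type I error 0.088: that figure needs both dropped dogs always to be non-responders and a cutoff re-derived to 3 of 8, and section 8 states neither a cutoff nor a re-derivation rule. The supported statement is that the denominator, and with it a borderline result, can depend on a discretionary, unmasked decision.

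**What to change.** - **Section 5.7.1, with 7.3.3 and 9.4 aligned:** state that missed or stopped IL-15 ends study drug only. The dog keeps its Day 35 and Day 49 visits and thoracic radiographs unless the owner declines or the clinician withdraws it for welfare or safety.
- **Section 5.7.2:** offer withdrawn dogs those two films first, with phone or email as the fallback. Record any other anticancer therapy and its start date, so that later films can be flagged.
- **Section 14.3:** state that these films and the sedation for them remain covered. The current text speaks only of enrolled dogs.
- **Owner consent:** add a matching line.

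Leave sections 7.3.1.2 and 7.3.1.3 as they are. Owners who want other treatment already have a withdrawal route. Allowing such treatment on study would confound the films and is not needed here.

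The cost is a short amendment and up to two films with sedation per affected dog, at visits already scheduled. Some owners will decline, and films taken after other therapy will be hard to attribute.

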#### 5.7.2 Data Collection and Follow-up for Withdrawn Subjects

Request permission for follow up phone calls or emails relating to outcome data. UCD can provide prepaid shipping label for return of nebulizer and supplies.

#### 5.7.3 Lost to Follow-up

Subjects are considered lost to follow-up if their caregivers fail to bring them to scheduled study visits and/or provide data and the caregivers cannot be reached by the study site. Attempts will be made once a month for 3 months by phone and email prior to being deemed LTFU.

CONFIDENTIAL

This material is the property of the University of California Do not disclose or use except as authorized in writing by the study sponsor

## 6 Study Investigational Product

### 6.1 Description

Recombinant Human Interleukin-15 (IL-15)-E. Coli product is described by the NCI Drug Dictionary as:

A recombinant agent that is chemically identical or similar to the endogenous cytokine interleukin-15 (IL-15) with immunomodulating activity. IL-15, secreted by mononuclear phagocytes (and some other cell types) following viral infection, regulates T and natural killer cell activation and proliferation. This cytokine induces activation of transcription activators STAT3, STAT5, and STAT6 via JAK kinase signal transduction pathways in mast cells, T cells, and dendritic epidermal T cells. IL-15 and interleukin-2 (IL-2) are structurally similar and share many biological activities; both may bind to common hematopoietin receptor subunits, negatively regulating each other's activity. CD8+ memory T cell number has been shown to be regulated by a balance between IL-15 and IL-2.

Standard commercially available doxorubicin administered and prepared as per typical UCD-VMTH protocol.

### 6.2 Treatment Regimen

All enrolled dogs are in the treatment group and will receive doxorubicin (30mg/m^2 or 1mg/kg depending on clinician prescription) IV on Day 0 and then 50ug inhaled IL-15 by nebulization twice daily x 14 days starting Day 7. No dose escalation to occur.

### 6.3 Assigning Subjects to Treatment Groups

N/A, single-arm study, no masking or randomization

### 6.4 Preparation and Administration of Investigational Product

A clinical trials coordinator will be responsible for the preparation and packaging of the IL-15

- This includes thawing and mixing the IL-15 and then drawing up into enough 6mL syringes for 14 days' worth at twice daily dosing
- The IL-15 will need to be packaged on ice for transport with care to avoid freeze/thaw.

A medical oncology staff member will be responsible for the preparation and administration of the doxorubicin.

#### 6.4.1 Special Handling Instructions

Personal Protective Equipment (PPE) Required for IL-15 Handling (trials personnel & client):

- Disposable chemotherapy gown, disposable N95 mask, eye protection, and gloves. (PPE will be sent home with the client)
- Should only be handled and administered in a well-ventilated area
- Once prepared, IL-15 must be stored at 4°C for up to 14 days

Personal Protective Equipment (PPE) Required for doxorubicin Handling (trials & VMTH personnel):

- Standard as per VMTH/medical oncology policies

CONFIDENTIAL

This material is the property of the University of California. Do not disclose or use except as authorized in writing by the study sponsor.

- Disposable chemotherapy gown, eye protection, and gloves.
- Should only be drawn up in the designated chemotherapy hood in medical oncology

## **6.5 Packaging**

See Appendix

## **6.6 Blinding of Investigational Product**

N/A

## **6.7 Receiving, Storage, Dispensing and Return**

### **6.7.1 Receipt of Investigational Product**

N/A

### **6.7.2 Storage**

IL-15 must be stored at 4°C for up to 14 days.

### **6.7.3 Dispensing of Investigational Product**

Clinical trials will be responsible for thawing and mixing the IL-15 and pulling up into 6mL syringes. The pharmacy will create a label: The script will be printed by the pharmacy and include:  
\*Refrigerate \* place 3mL of prepared drug into the nebulizer well. Administer twice a day over 10- 15 minutes until vapor is no longer seen, as demonstrated for owner, for 14 days. IL-15 will need to be packaged on ice for transport with care to avoid freeze/thaw.

### **6.7.4 Return or Destruction of Investigational Product**

See Appendix

CONFIDENTIAL

This material is the property of the University of California Do not disclose or use except as authorized in writing by the study sponsor

## 7 Study Procedures

### 7.1 Schedule of Events

| Procedure                               | Day -7 to -1   | Day 0          | Day 7          | Day 14 | Day 21 | Day 35 | Day 49 | Follow-up q8wks  |
|-----------------------------------------|----------------|----------------|----------------|--------|--------|--------|--------|------------------------------|
| Caregiver informed consent              | X              |                |                |        |        |        |        |                              |
| MDR Test in susc. breed                 | X              |                |                |        |        |        |        |                              |
| Screening echocardiogram                | X              |                |                |        |        |        |        |                              |
| Nebulizer demonstration with saline     | X              |                |                |        |        |        |        |                              |
| Nebulizer sent home for desensitization | X              |                |                |        |        |        |        |                              |
| Physical Examination                    | X              | X              | X              | X      | X      | X      | X      | X                            |
| Quality of Life Form                    | X              | X              | X              | X      | X      | X      | X      | X                            |
| CBC                                     | X  | X              | X              | X      | X      | X      |        |                              |
| Serum biochemistry                      | X  |                | X              |        | X      |        |        |                              |
| Urinalysis                              | X  |                |                |        | X      |        |        |                              |
| PBMCs                                   |                | X              | X              | X      | X      | X      |        |                              |
| Thoracic radiographs                    |                | X  |                |        |        | X      | X      | X                            |
| Doxorubicin administration              |                | X              |                |        |        |        |        |                              |
| IL-15 prepared and sent home with PPE   |                |                | X              |        |        |        |        |                              |
| IL-15 administration (at home)          |                |                | X  | X      |        |        |        |                              |

| Procedure                               | Day -7 to -1   | Day 0                | Day 7 | Day 14 | Day 21 | Day 35 | Day 49 | Follow-up q8wks  |
|-----------------------------------------|----------------|----------------------|-------|--------|--------|--------|--------|------------------------------|
| Caregiver informed consent              | X              |                      |       |        |        |        |        |                              |
| MDR Test in susc. breed                 | X              |                      |       |        |        |        |        |                              |
| Screening echocardiogram                | X              |                      |       |        |        |        |        |                              |
| Nebulizer demonstration with saline     | X              |                      |       |        |        |        |        |                              |
| Nebulizer sent home for desensitization | X              |                      |       |        |        |        |        |                              |
| Physical Examination                    | X              | X                    | X     | X      | X      | X      | X      | X                            |
| Quality of Life Form                    | X              | X                    | X     | X      | X      | X      | X      | X                            |
| CBC                                     | X  | X                    | X     | X      | X      | X      |        |                              |
| Serum biochemistry                      | X  |                      | X     |        | X      |        |        |                              |
| Urinalysis                              | X  |                      |       |        | X      |        |        |                              |
| PBMCs                                   |                | X                    | X     | X      | X      | X      |        |                              |
| Thoracic radiographs                    |                | X
(within 1 week) |       |        |        | X      | X      | X                            |

CONFIDENTIAL

This material is the property of the University of California. Do not disclose or use except as authorized in writing by the study sponsor.

|                                       |  |   |   |   |  |  |  |  |
|---------------------------------------|--|---|---|---|--|--|--|--|
| Doxorubicin administration            |  | X |   |   |  |  |  |  |
| IL-15 prepared and sent home with PPE |  |   | X |   |  |  |  |  |
| IL-15 administration (at home)        |  |   | X | X |  |  |  |  |

Should be performed within 7 days of Day 0, may occur outside of the UCD-VMTH.

Follow-up visits planned until Day 98, but may continue based on PI and client preference

Should be performed no more than one month before Day 0.

Initial IL-15 treatment will be done in the hospital to monitor patient. All subsequent treatments will be done at home.

